### Economic evaluation

In the present study we will also evaluate the outcome in the two study groups (Stop and Go) from a societal, economic perspective. It is therefore important to weigh cost savings for both groups against their clinical value. If relapse/recurrence incidence is within the predefined threshold (15 %), hence non-inferiority is confirmed; a straightforward cost minimization analysis will be executed focussing on cost savings. However, successful tapering of SSRIs will reduce SSRI use for years. Hence, with a sensitivity analysis on maternal effects and costs we will project cost estimations for 10 years. We expect that the upfront investment in PCT for women with previous psychiatric disorders will then be balanced by reduced SSRI use and less healthcare consumption. A previous RCT in a non-pregnant population demonstrated that a brief CT intervention is cost effective in remitted depressed individuals that stop antidepressants, compared to continuation of antidepressants [68].

If, however, relapse/recurrence incidence is higher than the predefined tolerance threshold, thus discontinuation is clinically inferior and rejected, a cost-effectiveness analysis will be executed as primary analysis, which estimates the costs avoided per additional relapse. This is the opposite of the extra costs per prevented relapse, if the starting point would have been no SSRI, and starting SSRI would be considered. Regardless the relapse outcome, we will conduct a cost utility analysis which estimates the impact of SSRI on the costs per Quality Adjusted Life Year (QALY), at least with a 3 month time horizon.

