### Trial objectives

In this randomized controlled trial (RCT), the effect of preventive cognitive therapy (PCT) with guided tapering of SSRIs in early pregnancy will be compared to continuation of SSRIs during pregnancy. We will study effects on both mother and child with a pragmatic approach. The expectation is that tapering of SSRIs with added PCT does not increase the risk of clinically relevant maternal relapse or recurrence^1^ of depression or onset of anxiety disorders during pregnancy up to three months postpartum in excess of [absolute] 15 % compared to continuation of SSRIs. If so, discontinuation is deemed non-inferior with regard to relapse/recurrence risk. Furthermore, we expect that tapering of SSRIs is better than continuation of SSRIs with respect to child development. Finally, but not unimportantly, we hypothesize that discontinuation will decrease total costs per woman and child on a 3 months and projected long term base, assuming no relevant effects of discontinuation on the mother and no effects on the child are found.

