### Randomisation

Two hundred women will be randomized in a 1:1 allocation ratio to either the intervention arm (STOP) or the care as usual arm (GO). Randomization will be done with a web based computer-generated randomization schedule (a validated TENALEA Clinical Trial Data Management System; http://www.formsvision.com/) using permuted blocks of random size with a maximum of 16 and stratified for the number of previous depressive episodes (dichotomized). Based on a recent review [35], the participants are divided into groups of participants with 3 or less previous depressive episodes, versus 4 or more. Allocation of participants is concealed for study researchers.

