### Sample size

Sample size calculation is based on the main aim of this study, which is to demonstrate non-inferiority of preventive CT with guided discontinuation of SSRIs (STOP) compared to continuation (GO), with respect to relapse or recurrence of a depressive episode up to 3 months postnatal. We will use a non-inferiority margin (tolerance threshold, ‘delta’) of 15 %. This is based on the assumption that this excess relapse (taking into account the possibility of restoring SSRI treatment) is still in balance with the expected beneficial effects of discontinuation of SSRI for the remaining mothers. We also anticipate that this balance is acceptable for women.

With this non-inferiority margin, and the assumption that the overall absolute risk of relapse will be around 15 % [67], we need 178 women, given alpha .025, power 80 %, and a one-sided test. To account for some attrition, we aim to include 200 women in total. Given this sample size, we have sufficient power to demonstrate small to moderate effect sizes of .42 or over on continuous secondary outcomes. With respect to dichotomous secondary outcomes, we will be able to detect odds ratios of 1.5 or over when the base probability is .5.

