### Statistical analysis

Analysis will primarily be carried out according to the intention-to-treat principle, i.e., the participants will be analysed according to their randomized allocation, regardless of the actual interventions received by the participant. Supplementary, we will perform analyses per protocol, i.e., according to actual SSRI use, irrespective of randomized arm.

The primary outcome, risk (cumulative incidence up to 3 months postnatal) of relapse of depression, will be compared between the randomized groups. Differences will be assessed statistically using a one-sided Chi-Square Test at a significance level of .025 and will be presented as a risk difference. The remainder of statistical tests will be performed two-sided at a significance level of .05.

Time to relapse will be compared between the randomized groups using survival analysis. Kaplan-Meier curves will be constructed and differences will be tested using the log-rank test. A Cox proportional hazard model will be used to calculate hazard ratios

Continuous outcomes, e.g., the General Movements scores at 3 months, will be compared between the groups using the unpaired *t*-test. Categorical secondary outcomes, e.g., obstetric complications, will be tested using Chi-Square Tests. For the continuous variables and categorical variables that are assessed more than twice, we will deploy linear mixed models and generalized linear mixed models respectively. These models use all available data (do not exclude persons with missing values) under the assumption of data being missing at random, and account for within-subject correlation over time. If despite randomization prognostically important factors differ between the groups, they will be adjusted for in supplemental analyses by including these factors in the pertaining regression models.

Subgroup analyses will be undertaken according to: Dutch/non-Dutch, nulliparous/multiparous, yes/no history depressive disorder and/or anxiety disorder, yes/no co-morbid anxiety symptoms or disorder. All effect parameters will be supplied with a 95 % confidence interval.

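### The economic section applies the 15 % non-inferiority margin without a confidence limit or an inconclusive outcome, so cost minimization can start before a 15-point excess has been excluded

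*Protocol article*

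**What the plan says.** All references are to the protocol article.

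- **Economic evaluation.** The pass branch reads: "If relapse/recurrence incidence is within the predefined threshold (15 %), hence non-inferiority is confirmed". Cost minimization then follows. In the fail branch, an incidence above the threshold means that discontinuation is called clinically inferior and is rejected, and cost-effectiveness becomes the primary economic analysis. A cost-utility analysis is run whatever the relapse result.
- **Trial objectives.** The threshold is comparative: the risk under tapering should not rise "in excess of [absolute] 15 % compared to continuation of SSRIs".
- **Sample size.** "We will use a non-inferiority margin (tolerance threshold, ‘delta’) of 15" %. The calculation uses "the assumption that the overall absolute risk of relapse will be around 15" %, and concludes: "we need 178 women, given alpha .025, power 80 %, and a one-sided test".
- **Statistical analysis.** The primary outcome is compared with a "one-sided Chi-Square Test at a significance level of .025 and will be presented as a risk difference". All effect parameters are to carry a 95 % confidence interval. The section mentions the margin in connection with neither.

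**The concern.** A non-inferiority conclusion needs sampling error on its side: the data must exclude an excess as large as the margin. The economic trigger compares a relapse result with 15 % directly and attaches the word confirmed to one side and inferior to the other. The two branches meet at a single number, which is how a point-estimate rule behaves. With a confidence limit there would be a third outcome, in which the interval contains the margin and neither statement is justified.

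The section that should settle the matter does not. A test level of .025 is given, but not the hypothesis it tests relative to 15 %, and the interval is promised without a decision attached. An analyst following the text could therefore run cost minimization, which sets aside any difference in effect, and the associated 10-year cost projection, in a trial that has not excluded a 15-point excess of relapse. In the other direction, an imprecise result slightly above 15 points would be reported as proof of inferiority.

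**Working it through.** **Inputs.** Margin 15 percentage points on STOP minus GO (Trial objectives, Sample size); assumed relapse risk 15 %, one-sided alpha .025, power 80 %, 178 women (Sample size); 1:1 allocation of 200 women (Randomisation). Hence 89 per arm before the attrition allowance and 100 per arm at full enrolment.

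**Step 1: reproduce the plan's sample size.** For a test against the margin with equal true risks p and unpooled variance,

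n per arm = (1.960 + 0.842)² × 2p(1 − p) / margin² = 7.849 × 2 × 0.15 × 0.85 / 0.15² = 88.95, rounded up to 89.

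Twice 89 is 178, the stated figure. The trial was thus sized for a one-sided .025 test against the margin. That is the same as requiring the upper limit of a two-sided 95 % interval to lie below 15 points.

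**Step 2: define the two rules.** With observed risks a (GO) and b (STOP) and n per arm:

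- Observed-difference rule: pass if b − a is within 0.15.
- Upper-limit rule: pass if b − a + 1.96 × √[a(1 − a)/n + b(1 − b)/n] < 0.15.

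**Step 3: exact probabilities.** All pairs of binomial counts were enumerated with a true GO risk of 15 %. At 89 per arm an observed difference of exactly 15 points cannot occur (0.15 × 89 = 13.35 events), so ≤ and < agree. At 100 per arm it can occur, and both versions are shown.

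| True excess (points) | Observed difference, 89 | Upper limit, 89 | Observed difference, 100 (< to ≤) | Upper limit, 100 |
|---|---|---|---|---|
| 0 | 99.8 % | 80.1 % | 99.8 to 99.9 % | 84.3 % |
| 5 | 96.3 % | 42.5 % | 96.2 to 97.5 % | 46.4 % |
| 10 | 80.8 % | 13.5 % | 78.9 to 83.7 % | 14.6 % |
| 15 (the margin) | 51.1 % | 2.6 % | 46.6 to 53.4 % | 2.6 % |
| 20 | 22.2 % | 0.3 % | 17.8 to 22.5 % | 0.3 % |

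With no true excess, the upper-limit rule at 89 per arm passes in 80 % of trials, the planned power. The observed-difference rule passes nearly always, so it is not the rule on which the sample size rests.

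**Step 4: vary the assumed GO risk.** Over an assumed range of 7.5 % to 26 %, with the true excess at the margin, the observed-difference rule passes in 50.8 to 51.5 % of trials at 89 per arm and in 46 to 54 % at 100 per arm. The upper-limit rule passes in about 2.5 to 3.0 %.

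**Step 5: one data set.** Suppose GO shows 15 % and STOP 30 %, with 89 per arm. The standard error is √(0.15 × 0.85/89 + 0.30 × 0.70/89) = 0.0616, so the 95 % interval is 0.15 ± 0.121, or 2.9 to 27.1 points. This result sits on the boundary between the two branches of the economic section, although the data exclude neither a small excess nor one far above the margin. With GO observed at 15 %, the upper-limit rule needs an observed excess below about 4.0 points (89 per arm) or 4.5 points (100 per arm).

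**Step 6: the fail branch.** With the true excess at the margin and 89 per arm, the observed difference exceeds 15 points in 100 − 51.1 = 48.9 % of trials, but the lower 95 % limit exceeds 15 points in only 2.65 %. In about 46 % of trials the inferior label would thus rest on an interval that still contains the margin.

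**The case against.** **The sentence may be shorthand.** It can be read as a summary of the primary comparison, with the test assumed. The Trial objectives section uses similar shorthand, and a condensed article may leave the operational trigger to a fuller document. This would carry weight if the Statistical analysis section gave the full rule, but it does not link its test or its interval to the margin. The fail branch also resists this reading: under a test against the margin, failing to show non-inferiority is not evidence of inferiority, yet the text equates the two. What stands is that the observed-difference reading is the natural one, not the only one, and the figures above depend on it.

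**A rate near one half is generic.** Any point-estimate rule passes about half the time at its own boundary. That is true; the figure measures what the reading costs and does not prove the reading.

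**Two stronger readings that the documents do not support.**

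- A reader might infer that STOP's own incidence is to be compared with 15 %, since the sentence names no comparator and the assumed risk is also 15 %. But the section calls the threshold predefined and a tolerance threshold, and the Sample size section defines that term as the non-inferiority margin for STOP against GO. The missing comparator is a fault of wording only.
- A reader might infer that the primary analysis has a type I error near 50 %. The sentence formally selects the economic analysis; the primary test is set out elsewhere at .025.

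**A safeguard exists.** The cost-utility analysis is run regardless of the relapse result, so costs and quality-adjusted life years are assessed in either branch. This softens the consequence but does not correct the label or the choice of the other analysis.

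**Conclusion.** The point holds for the economic trigger and is wrong as written. The threshold is the absolute STOP minus GO margin, but it is applied with no confidence limit and no inconclusive outcome, and the Statistical analysis section does not supply the missing link.

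Read as an observed difference, with a GO risk of 15 % and a true excess at the margin, the trigger would start cost minimization in 51 % of trials (89 per arm) or 47 to 53 % (100 per arm, depending on whether exactly 15 points counts as within), against 2.6 % under an upper-95 %-limit rule. The contrast changes little over GO risks from 7.5 % to 26 %. It assumes independent binomial outcomes, equal arms and complete follow-up. No section of the article states a confidence-limit rule; the upper-limit rule is proposed because it corresponds to the test that reproduces the 178 women.

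**What to change.** 1. In the Economic evaluation section, and in the same words in the Statistical analysis section, state: non-inferiority is concluded only if the upper limit of the two-sided 95 % confidence interval for risk(STOP) minus risk(GO) is below 15 percentage points.
2. Start the cost-minimization analysis only when this is met. Otherwise run the cost-effectiveness analysis as the primary economic analysis. The cost-utility analysis stays as planned.
3. In the fail branch, replace the statement that discontinuation is inferior with: non-inferiority not shown. Keep a statement of inferiority beyond the margin for the case in which the lower limit exceeds 15 percentage points.

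The cost is a few sentences of text. The sample size, the data collected and the conduct of the trial do not change.

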## Discussion

The use of SSRIs during pregnancy remains a clinical dilemma for both clinicians and patients. Given the increase of SSRI use among pregnant women and studies reporting conflicting results [7, 8, 11–14, 18, 19], there is dire need of randomized controlled trials investigating the use of SSRIs during pregnancy. This study will be the first to investigate the effect of preventive cognitive therapy with guided tapering of SSRIs from early pregnancy onwards as compared to continuation of SSRIs during pregnancy. Additionally, the study focuses on child outcomes and cost effectiveness.

Previous studies on relapse prevention showed promising results for tapering antidepressants with added relapse prevention [29]. Preventive cognitive therapy moreover showed promising long-term effects in non-pregnant women with a history of depression [27, 28]. Preventive cognitive therapy with guided tapering of antidepressants may therefore be a good alternative for SSRI use during pregnancy.

To our knowledge, no randomized controlled trials have been performed during pregnancy that investigated alternative treatment options versus SSRI use. This may be the result of the complex ethical situation of studies in pregnant women who are taking SSRIs and must be willing to either taper or continue SSRI use. Logistics of a nationwide randomized controlled trial are also difficult in a multidisciplinary setting. Although a multidisciplinary guideline exists, health care givers still have different views on best practice and therefore give different advices to their patients. This study will therefore be as pragmatic as possible, while still providing the intervention in a protocoled manner.

Results of this study will be published and will contribute to further development of (international) guidelines. The results will provide a first step in giving pregnant women an answer to the question whether it is better to stop or to continue the use of SSRIs during pregnancy.

## Ethics approval and consent to participate

The Medical Ethical Commission of the Erasmus Medical Center approved this study. Participants will sign informed consent form before participation.

## Abbreviations

BMQ: beliefs about medicines questionnaire
CBT: cognitive behavioural therapy
CJG: centres for childhood
CRF: case report form
CTQ: childhood trauma questionnaire
C-TRF: caregiver teacher report form
DAS: dysfunctional attitude scale
DESS: discontinuation emergent signs and symptoms checklist
EPCL: everyday problem checklist
EPDS: Edinburgh postnatal depressions scale
EQ-5D-5L: quality of life questionnaire
GM: general movements
HDRS: Hamilton depression rating scale
I-PANAS-SF: International short-form of the positive and negative affect schedule
LDS: language development survey
MARS: medication adherence rating scale
PCT: preventive cognitive therapy
PPHN: persistent pulmonary hypertension of the neonate
QALY: quality adjusted life year
RCT: randomized controlled trial
SCID-1: structured clinical interview for DSM-disorders axis 1
SSRI: selective serotonin reuptake inhibitors
STAI: State trait anxiety inventory
